### Strengths and limitations

This RCT will provide evidence of the use of CFT in individuals with shoulder pain. The methods follow established guidelines for conducting and reporting trials, with an appropriate sample size calculation to provide statistical power in all outcomes, blinded assessor, and stratified randomization process. The authors have significant experience in developing and delivering interventions involving CFT and conducting RCTs with patients with shoulder pain. Therapists providing CFT will receive appropriate training and supervision to ensure proper delivery of the intervention [83]. The comparator group, therapeutic exercises, follows current best practices, offering a fair comparison to CFT. Additionally, the study focuses on patients with high levels of disability, a population that typically reports lower levels of improvement after rehabilitation [43], adding further relevance to our findings. Therefore, we believe this study will contribute to the best practice evidence for treating patients with shoulder pain.

A key limitation is the inability to blind therapists and participants due to the nature of the intervention. Both will need to be aware of the study’s objectives and treatments. Finally, another limitation is that CFT, like therapeutic exercise, lacks established parameters and dosage, as the research on CFT is still recent.

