The calculation was based on an estimated mean difference of 18 points [41] (standard deviation of 24.6) [42] in shoulder disability, assessed with Shoulder Pain and Disability Index (SPADI), with a two-tailed significance set at 0.05, power at 80%, and accounting for a 15% dropout, which resulted in 36 individuals per group for a total of 72 individuals. The sample size, calculated based on pain intensity (a mean difference of 2 points and a standard deviation of 2.5 on the NPRS), resulted in a total sample of 48 individuals. Therefore, the sample size calculation for this study was based on shoulder disability.

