### Data analysis

Statistical analysis will be conducted using the Statistical Package for the Social Sciences (SPSS) version 24.0 or a more recent version (SPSS Inc., Chicago, IL). Continuous data will be summarized as means ± standard deviation (SD) and 95% confidence intervals (CIs). Data normality will be assessed through visual inspection of histograms and the Shapiro-Wilk test. The analysis will adhere to the intention-to-treat principle. Between-group differences (treatment effects) and their corresponding 95% CIs will be computed using linear mixed models with Bonferroni adjustments. If non-normality of the data is identified, transformations will be performed as needed or generalized linear mixed models will be considered. Fixed effects will include group, time, and the group-by-time interaction. Random effects will account for individual variability. A significance level of 0.05 will be applied for all statistical tests.

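### The claim of power in all outcomes is unsupported: only SPADI and NPRS were calculated, at an unadjusted 0.05 that may not be the level of the planned analysis

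*Protocol article*

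**What the plan says.** The Sample section bases the calculation on "an estimated mean difference of 18 points [41] (standard deviation of 24.6) [42] in shoulder disability". The error rates and attrition are set out there as "with a two-tailed significance set at 0.05, power at 80%, and accounting for a 15% dropout". From these inputs the article arrives at 36 participants per arm, 72 in all. A second calculation, on "a mean difference of 2 points and a standard deviation of 2.5 on the NPRS", gave a smaller total of 48. The section concludes: "Therefore, the sample size calculation for this study was based on shoulder disability". No other outcome is calculated.

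Table 2 lists as secondary outcomes the PSFS, PSEQ, PSQI, the brief biopsychosocial screening questions, the global rating of change, and three central pain processing measures (pressure pain threshold, temporal summation, conditioned pain modulation).

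The Data analysis section says that between-group differences and their 95% confidence intervals "will be computed using linear mixed models with Bonferroni adjustments". It does not say which comparisons the adjustment covers. It also sets a significance level of 0.05 for every test.

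The Strengths and limitations section then lists as a strength an "appropriate sample size calculation to provide statistical power in all outcomes".

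**The concern.** Two statements do not fit the calculation on which they rest.

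First, power is a property of a given outcome with a given difference and standard deviation. The article supplies these for two outcomes and claims power for all of them. The Introduction hypothesises that CFT is superior across the whole set. A reader who accepts the claim may therefore take a null result on sleep, self-efficacy or pain processing as evidence of no effect, when the trial may have had little chance of detecting one.

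Second, the 80% for SPADI is calculated for one test at 0.05. If the planned Bonferroni adjustment applies to the between-group SPADI contrast, the level is smaller and so is the power.

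**Working it through.** **Inputs.** From the Sample section: SPADI difference 18, SD 24.6; NPRS difference 2, SD 2.5; two-sided alpha 0.05; power 80%; dropout 15%. From Randomization: 1:1 allocation. From the Abstract and Procedures: two primary outcomes and three post-baseline visits (weeks 4, 8 and 12).

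**Reproducing the stated size.** With r = 1 the article's formula is n = 2(z₀.₈₀ + z₀.₉₇₅)²σ²/d² per arm.

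- SPADI: 2 × (0.8416 + 1.9600)² × 24.6²/18² = 29.3, so 30 per arm. Then 30/0.85 = 35.3, so 36 per arm and 72 in total. This matches the article.
- NPRS: 2 × (0.8416 + 1.9600)² × 2.5²/2² = 24.5, so 25 per arm and 50 in total before dropout, close to the stated 48. SPADI governs the size either way.

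So 72 is the size for one SPADI comparison at an unadjusted 0.05.

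**What 72 participants can detect on any outcome.** With 30 completers per arm, the standardised difference detectable with 80% power at 0.05 is 2.8016 × √(2/30) = 0.72. The two calculated outcomes exceed it: SPADI 18/24.6 = 0.73 and NPRS 2/2.5 = 0.80. For smaller effects (noncentral t, 30 per arm, alpha 0.05):

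| Assumed standardised difference | Power |
|---|---|
| 0.5 | 48% |
| 0.3 | 21% |

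The values 0.5 and 0.3 are assumptions for illustration. The article gives no expected effect for any secondary outcome.

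**SPADI power if Bonferroni covers k comparisons.** Normal approximation: Φ(d/(σ√(2/n)) − z₁₋α/₂ₖ). With n = 30, d/(σ√(2/n)) = 0.7317 × √15 = 2.834. For k = 2 this is Φ(2.834 − 2.241) = 72%. The t column is the noncentral t with 58 degrees of freedom.

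| k | Alpha | Power (t) | Power (normal) |
|---|---|---|---|
| 1 | 0.05 | 80% | 81% |
| 2 (for example, two primary outcomes) | 0.025 | 70% | 72% |
| 3 (for example, three visits) | 0.0167 | 64% | 67% |
| 6 (for example, two outcomes × three visits) | 0.0083 | 54% | 58% |

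With no dropout (36 per arm), power at k = 2 is 79% (t) or 81% (normal). The values of k are assumptions, because the article does not state one.

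**The case against.** The strongest objection concerns the Bonferroni part. A reader might infer that SPADI power under the planned analysis is simply 64–72%. The documents do not support that. The Data analysis section names no family, and defining one is commonly left to an analysis plan, so its absence is not a fault in itself. The same section sets 0.05 for all tests. With two groups there is one between-group contrast per visit; if the adjustment serves only comparisons between visits within the model, that contrast keeps its full 0.05 and the 80% holds. The 64–72% range also takes its ends from different methods: 64% is the t figure for three comparisons and 72% the normal figure for two.

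The power model is also simple: one visit, two samples, completers only. The planned intention-to-treat mixed model can use partial data from participants who drop out, and a gain in precision from baseline could raise power further, although the article describes no such gain. These points stand. They make the loss of power conditional.

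They do not rescue the claim of power in all outcomes. That is a positive statement, and the article's own calculation covers two outcomes only. It is true that between-group differences with 95% confidence intervals are already planned, which limits the harm, but the published assurance would still invite misreading of null results.

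**Conclusion.** The claim of power in all outcomes is not supported and should be withdrawn. This holds whatever the Bonferroni family turns out to be. The design has 80% power only for standardised differences of about 0.72 or more, assuming 15% dropout and a test at 0.05, and the article makes no such assumption for any secondary outcome.

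The arithmetic behind 72 is correct. The 80% for SPADI is right if the between-group SPADI contrast is tested at 0.05, and overstated under the article's own dropout assumption if the adjustment covers two or more comparisons. The possible values run from about 80% with no adjustment down to 54–58% with six comparisons. Which applies cannot be read from the article. What can be said is that the alpha used for sizing and the adjustment described for the analysis have not been tied together.

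**What to change.** In Strengths and limitations, limit the claim to SPADI, with NPRS also calculated. Say that the trial is not powered for the secondary outcomes, which are reported as estimates with 95% confidence intervals.

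In Sample, state SPADI power at the alpha that will actually be used for the primary between-group contrast. If that contrast is unadjusted, keep 80% and say so. If Bonferroni covers the two primary outcomes, restate power as about 70% at 0.025. For any other family, use the matching figure.

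The cost is a text change in two places, and one stated figure may become less favourable. No change in sample size is needed, and the two primary outcomes need not be re-ranked.
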